Recently, Ye *et al* performed a meta-analysis of 10 studies that indicated that IVUS-guided percutaneous coronary intervention (PCI) of the LMCA reduced the risk of all-cause mortality by 40% and cardiac death by 53% compared with conventional angiography-guided procedures. In addition, IVUS-guided PCI was associated with lower risks of target lesion revascularization and stent thrombosis. Of the included studies, one was a small randomized trial; the others were either single or multicenter registries. The primary endpoint – all-cause mortality – was reported in nine studies; and cardiac mortality was reported in six studies. IVUS-guidance was associated with lower risks of target lesion revascularization (relative risk (RR) 0.43, 95% confidence interval (CI) 0.25–0.73,  $p=0.002$ ) and definite or probable stent thrombosis (RR 0.28, 95% CI 0.12–0.67,  $p=0.004$ ), but not MI or target vessel revascularization.

While most of the studies included in both meta-analyses had a significant number of distal LMCA lesions, only the propensity-score matched IVUS-TRONCO-ICP Spanish study looked at this subgroup specifically. In the subgroup of distal lesions irrespective of treatment, IVUS-guidance reduce the composite of death, MI and target lesion revascularization from 19% to 11% ( $p = 0.03$ ), a difference that was magnified in distal LMCA lesions treated with two stents (41.0% to 16.7%,  $p = 0.02$ ). Most recently, Andell *et al* have reported a reduced incidence of a combined primary endpoint of mortality, stent thrombosis and restenosis over a period of five years when LMCA intervention was guided by IVUS.

Nevertheless, there is data suggesting higher volume PCI operators are likely to get better outcomes for patients with LMCA disease. These single center data did not show a benefit from IVUS, and this replicates some historical data where IVUS imaging in every case was not clearly supported by data. Of note, the EBC recommended IVUS in LMCA in all elective cases especially when clinical practice is evolving and when procedural complications occur.

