## 6. Study endpoints

### Primary endpoint:

Patient-oriented Composite Endpoint (PoCE): all-cause death, any stroke, any myocardial infarction (MI)\*, any repeat revascularization at 2 years follow-up.

\*SCAI definition for peri-procedural MI ; 4th universal definition for spontaneous (>48 hours) MI .

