### Secondary endpoints:

1. Device-oriented Composite Endpoint (DoCE) defined as the composite of: cardiovascular death, target-vessel MI, clinically indicated repeat revascularization of the target lesion;
2. Vessel-oriented Composite Endpoint (VoCE) defined as the composite of: cardiovascular death, target vessel MI, repeat revascularization of the target vessel;
3. PoCE at 1 year
4. All-individual components of PoCE;
5. All individual components of DoCE;
6. All individual components of VoCE;
7. Definite and probable stent thrombosis according to ARCII definition;
8. Investigator reported hospitalization for heart failure.

Note: All endpoints will be reported at 1 and 2 years.

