### 8.2. Statistical analysis

The statistical analysis of the primary endpoint is confirmatory. The statistical analysis of the secondary endpoints is exploratory. This section indicates how the primary endpoint and the clinical secondary event points are analyzed.

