#### 8.2.1. Time dependent endpoints

Analysis of clinical primary and secondary endpoints will be performed. Two types of time-to-event, Kaplan-Meier (KM), analyses are performed. When the KM-curves for the IVUS guidance arm and the Angio Guidance arm are compared the regular KM-analysis is performed to compare the survival distributions of the two arms, using the log-rank test. This method is non-parametric.

Additionally the KM-estimates for the two arms at a single fixed time point  $\tau$  (1 month, 12 months, 24 months) are compared, thus disregarding the shape of the survival curves up to time point  $\tau$ . In this analysis the Com-Nougue approach will be applied.

In the Com-Nougue approach the survival proportion at time point  $\tau$  is calculated for both arms.

A 95% Confidence interval and two-sided p-value will be calculated for the Risk Difference, being the difference in these survival proportions, are constructed using the Greenwood Standard Error of the survival proportions, as estimated by KM-analysis. In the calculation the complement of the survival proportions is used, measuring the incidence of the reported event.

No standard SAS procedure is available for this analysis, the analysis is therefore specified in this section.

The Risk Difference (RD) is the difference between the two KM-estimates:

$$(1) \quad RD = KM_{\text{Ivus Guidance}} - KM_{\text{Angio Guidance}}$$

A positive Risk Difference ( $RD > 0$ ) indicates a higher event rate for the Ivus Guidance arm than for the Angio Guidance arm, a negative Risk Difference ( $RD < 0$ ) indicates a lower event rate for the Ivus Guidance arm than for the Angio Guidance arm

The standard error of the Risk Difference is calculated as:

$$(2) \quad SE_{RD} = \sqrt{SE^2_{\text{Ivus Guidance}} + SE^2_{\text{Angio Guidance}}}$$

A 95% confidence interval ( $CI_{RD,95\%}$ ) is calculated for the risk difference by applying the standard normal distribution:

$$(3) \quad CI_{RD,95\%} = [RD - Z_{0.975} * SE_{RD}, RD + Z_{0.975} * SE_{RD}]$$

where  $Z_{0.975}$  is the value of the standard normal distribution which has an upper tail probability of 2.5%, this value is around +1.96.

The p-value for the superiority test is the two-sided p-value for the difference between the Risk Difference in the trial (RD) and the assumed difference under the Null Hypothesis ( $H_0: RD=0$ ):

$$(4) \quad Z_{RD} = (RD - 0) / SE_{RD} = RD / SE_{RD}$$

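### Section 8.2.1 treats 1 minus Kaplan-Meier as incidence for secondary endpoints that omit all-cause death; there it slightly overstates each arm's rate and can shift the difference either way

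*Protocol*

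**What the plan says.** Section 8.2 sets its scope: "This section indicates how the primary endpoint and the clinical secondary event points are analyzed". Section 8.2.1 repeats it: "Analysis of clinical primary and secondary endpoints will be performed". Two comparisons follow. One is a log-rank test on the KM curves. The other is a fixed-time comparison at 1, 12 and 24 months (the Com-Nougue approach), in which the risk difference, its confidence interval and its p-value come from the two KM estimates and their Greenwood standard errors, through formulas (1) to (5). On what is being estimated, the section states: "In the calculation the complement of the survival proportions is used, measuring the incidence of the reported event". Cox models are named for any hazard ratios.

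Section 6 lists the endpoints. The primary is "Patient-oriented Composite Endpoint (PoCE): all-cause death, any stroke, any myocardial infarction" and repeat revascularization. The secondary list includes DoCE ("cardiovascular death, target-vessel MI, clinically indicated repeat revascularization of the target lesion"), VoCE, PoCE at 1 year, every single component of the three composites, "Definite and probable stent thrombosis according to ARCII definition" and heart-failure hospitalization. All are reported at 1 and 2 years.

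Section 8.2 also states: "The statistical analysis of the secondary endpoints is exploratory". The protocol mentions neither competing events nor a cumulative incidence function. Section 8.2.1 leaves further method details to a SAP.

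**The concern.** The complement of a KM curve equals the proportion of patients who have the event only if nothing but administrative censoring or loss to follow-up removes them from risk. A patient who dies cannot later have a stroke or a stent thrombosis. Censoring that patient at death makes KM act as if the patient could still have the event at the same rate as those alive. The result is the risk in a hypothetical population without the competing death, and it is at least as large as the real incidence.

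The component rates and differences will be read as observed incidences and used to explain any PoCE result. If mortality differs between arms, the upward error differs too and enters the risk difference. The Greenwood standard error in formula (2) then belongs to the hypothetical quantity, as do the interval and p-value built on it.

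**Working it through.** **Step 1: where death competes.**

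| Endpoint (section 6) | Competing death | 1-KM is incidence? |
|---|---|---|
| PoCE at 1 and 2 years; all-cause death | none | yes |
| DoCE, VoCE, cardiovascular death | non-cardiovascular only | no, small error |
| Stroke, MI, revascularization, target-vessel MI, target-lesion and target-vessel revascularization, stent thrombosis, heart-failure hospitalization | any death | no |

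The Appendix counts undetermined deaths as cardiovascular, which further narrows the deaths that compete in the second row.

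**Step 2: inputs and formula.** The protocol gives no figure for this point to reproduce, and no expected mortality or component rates. The following are therefore assumptions: 2-year competing mortality D of 2% to 10%, event rates of 1% to 10%, and constant, independent cause-specific hazards.

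Let K be the 2-year 1-KM value, H = -ln(1-K) and G = -ln(1-D). The cumulative incidence is

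CIF = H/(H+G) × (1 - exp(-(H+G))).

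Example with K = 10% and D = 6%: H = 0.1054, G = 0.0619, H/(H+G) = 0.630, and 1 - exp(-(H+G)) = 1 - 0.90 × 0.94 = 0.154. CIF = 0.630 × 0.154 = 9.70%, so 10% is too high by 3.1% in relative terms.

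**Step 3: error within one arm (K = 10%).**

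| D | 2% | 4% | 6% | 8% | 10% |
|---|---|---|---|---|---|
| CIF | 9.90% | 9.80% | 9.70% | 9.60% | 9.50% |
| 1-KM too high by (relative) | 1.0% | 2.0% | 3.1% | 4.2% | 5.3% |

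Read the other way, a true incidence of 10% appears as 10.1% (D = 2%) to 10.5% (D = 10%). The relative error hardly depends on the event rate: over the same range of D, K = 3% corresponds to 2.97% to 2.85%, and K = 1% to 0.99% to 0.95%. For DoCE or VoCE with an assumed 2% to 4% non-cardiovascular death, K = 10% corresponds to 9.90% to 9.80%.

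**Step 4: error in the difference (IVUS minus angio, in points).**

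| K, IVUS vs angio | D, IVUS vs angio | KM difference | CIF difference |
|---|---|---|---|
| 6.5% vs 10% | 6% vs 6% | -3.50 | -3.40 |
| 6.5% vs 10% | 4.8% vs 8% | -3.50 | -3.26 |
| 6.5% vs 10% | 8% vs 4.8% | -3.50 | -3.52 |
| 10% vs 10% | 4.8% vs 8% | 0.00 | +0.16 |
| 10% vs 10% | 8% vs 4.8% | 0.00 | -0.16 |

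When mortality is lower with IVUS (rows 2 and 4), KM favours IVUS by 0.24 and 0.16 points. When it is higher (rows 3 and 5), KM works against IVUS by 0.02 and 0.16 points.

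**Step 5: scale.** For 6.5% vs 10% with 400 per arm, the standard error of the difference is about sqrt((0.065 × 0.935 + 0.10 × 0.90)/400) = 1.94 points. The largest error in the table, 0.24 points, is about one eighth of that.

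**The case against.** The strongest defence is that little depends on this. The affected endpoints are exploratory. The superiority rule in section 8.2.1 concerns only the primary endpoint, where 1-KM is right. The error is small against sampling error. Log-rank and Cox analyses with death censored remain valid comparisons of cause-specific hazards. All of this stands, and it sets the severity.

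It can also be said that competing-risk handling belongs in the SAP, which is not shown. That holds for a method the protocol leaves open. Here the protocol itself fixes the estimator, its standard error and its interpretation as incidence, so the statement is wrong as written for most of the listed endpoints.

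A reader might infer more than the documents support:

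- **That every secondary endpoint is affected.** PoCE at 1 year and all-cause death are not, and DoCE, VoCE and cardiovascular death only slightly.
- **That differences are always inflated in favour of IVUS.** Step 4 shows no fixed sign.
- **That the plan expects a large mortality benefit, which settles the direction.** The Introduction reports that in a cited meta-analysis, mostly of registries, IVUS guidance "reduced the risk of all-cause mortality by 40% and cardiac death by 53" per cent. Section 8.3 assumes a 35% reduction in PoCE and nothing about mortality.
- **That differences could be overstated by about 12%.** This needs, for example, a true component incidence of 15% (angio) vs 10% (IVUS) with mortality of 12% vs 7.2%. Then 1-KM gives 15.95% vs 10.37%, a difference of -5.6 instead of -5.0 points. But event or death would be 1 - 0.8405 × 0.88 = 26.0% vs 1 - 0.8963 × 0.928 = 16.8%. That uses up almost the whole planned PoCE of 26% vs 17% and leaves next to nothing for the other components.

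**Conclusion.** The point holds for secondary endpoints that do not include all-cause death: section 8.2.1 names as incidence a quantity that is not incidence. For an assumed 2-year competing mortality of 2% to 10% and constant hazards, the arm-level overstatement is about 1% to 5% in relative terms, at most about half a point for an endpoint near 10%. The error in the difference is up to a few tenths of a point; its sign depends on which arm has the higher mortality and on the event rates. Severity is low: the endpoints are exploratory, and neither the confirmatory PoCE analysis nor the sample size is touched. It is still worth correcting, because these rates will be published as incidences and the correction is cheap.

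**What to change.** In section 8.2.1 and the SAP:

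- Limit the sentence equating the KM complement with incidence to PoCE and all-cause death, and keep KM with Greenwood standard errors for those two.
- For every other clinical endpoint, use the Aalen-Johansen cumulative incidence at each fixed time, and put its estimate and variance into formulas (1) to (5). The competing event is death from any cause; for DoCE, VoCE and cardiovascular death it is non-cardiovascular death as adjudicated.
- Describe log-rank and Cox results for those endpoints as comparisons of cause-specific hazards.

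The cost is a change of wording and some programming with standard software. Deaths and their adjudicated cause are already part of the trial's endpoints, so no new data, visits or patients are needed.

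### Section 8.2.1 applies the untransformed Greenwood/normal interval to every clinical endpoint; it breaks down when an arm has no events and can be too short when an arm expects about one event or fewer

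*Protocol*

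**What the plan says.** Protocol section 8.2 sets the scope: "This section indicates how the primary endpoint and the clinical secondary event points are analyzed". Section 8.2.1 repeats that both primary and secondary clinical endpoints are meant, and describes two Kaplan-Meier analyses. In the first, "the regular KM-analysis is performed to compare the survival distributions of the two arms, using the log-rank test". The second compares the two estimates at a fixed time of 1, 12 or 24 months. Its interval and p-value "are constructed using the Greenwood Standard Error of the survival proportions, as estimated by KM-analysis". Formula (2) takes the root of the summed squared standard errors. Formula (3) forms the 95% interval, which "is calculated for the risk difference by applying the standard normal distribution". Formulas (4) and (5) give a two-sided Z test.

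The protocol presents this as a complete prescription: "No standard SAS procedure is available for this analysis, the analysis is therefore specified in this section".

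Section 6 lists the secondary endpoints. They include "Definite and probable stent thrombosis according to ARCII definition" and each separate component of the three composites, such as stroke. All are to be reported at 1 and 2 years. Section 8.2 calls the secondary analyses exploratory. The end of 8.2.1 limits the superiority rule to the primary endpoint and leaves further detail to a statistical analysis plan. Section 8.3 gives 400 participants per arm.

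**The concern.** A Greenwood/normal interval is sound for an endpoint expected in 17% and 26% of participants. It depends on each arm having enough events for its own variance to be estimated. With none, Greenwood's variance is exactly zero, so the calculation treats that arm's risk as known to be 0 and takes all its width from the other arm. With none in either arm, formula (4) divides zero by zero.

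At stake are the intervals for stent thrombosis and for infrequent components, especially at 1 month. No confirmatory test applies to these endpoints, so the interval is the main information a reader receives. If the method is not settled in advance, it would have to be chosen after a zero cell has been seen.

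**Working it through.** **Inputs.** n = 400 per arm (section 8.3) and formulas (2) to (5) (section 8.2.1). The protocol gives no expected rate for stent thrombosis, stroke or any 1-month component, and no figure of its own to reproduce on this point. All rare-event rates below are therefore assumptions, shown as a range. Without early censoring, the Greenwood standard error is sqrt(p(1-p)/n).

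**Step 1: no events in one arm (0 versus 4 of 400).**
- SE(IVUS) = 0. SE(angio) = sqrt(0.01 × 0.99/400) = 0.004975, so SE(RD) = 0.004975.
- Interval: -0.01 ± 1.96 × 0.004975, or -1.98 to -0.02 points. Z = 2.01, p = 0.044.
- Newcombe comparator, from single-arm Wilson limits: 0/400 gives 0 to 0.951%, and 4/400 gives 0.390 to 2.543%. Lower limit: -1 - sqrt(0² + 1.543²) = -2.54. Upper limit: -1 + sqrt(0.951² + 0.610²) = +0.13.

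**Step 2: no events in either arm.** SE(RD) = 0, the interval is [0, 0] and Z = 0/0. Newcombe gives -0.95 to +0.95 points.

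**Step 3: how often a zero arm occurs.** At a true risk of 0.25%, one arm has no events with probability (1 - 0.0025)^400 = 37%. With equal risks, at least one arm is empty in 60% of trials at 0.25%, 25% at 0.5% and 3.6% at 1%.

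**Step 4: coverage.** Exact summation over all pairs of binomial counts, 400 per arm:

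| True risks (%) | Expected events | Stated interval | Newcombe |
|---|---|---|---|
| 0.1 vs 0.25 | 0.4 vs 1 | 74.8% | 99.9% |
| 0.1 vs 0.5 | 0.4 vs 2 | 86.2% | 99.6% |
| 0.25 vs 0.5 | 1 vs 2 | 85.8% | 99.1% |
| 0.25 vs 0.75 | 1 vs 3 | 93.4% | 99.1% |
| 0.25 vs 1 | 1 vs 4 | 89.8% | 97.8% |
| 0.5 vs 0.75 | 2 vs 3 | 92.7% | 97.8% |
| 0.5 vs 1 | 2 vs 4 | 94.6% | 98.0% |
| 0.5 vs 1.5 | 2 vs 6 | 94.0% | 96.4% |
| 1 vs 2 | 4 vs 8 | 95.0% | 96.0% |
| 0.25, both arms | 1 vs 1 | 98.6% | 99.7% |
| 0.5, both arms | 2 vs 2 | 95.9% | 98.3% |
| 1, both arms | 4 vs 4 | 95.4% | 96.4% |
| 17 vs 26 (primary) | 68 vs 104 | 94.9% | 95.0% |

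With 376 per arm (6% attrition) the pattern is the same; for example, 84.6% at 0.1 vs 0.5% and 91.5% at 0.25 vs 1%. Coverage moves unevenly between neighbouring pairs because the counts are so small.

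**Step 5: type I error of the Z test.** For equal risks from 0.1% to 4%, it peaks at about 5.2%.

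**The case against.** The strongest reply is that this is a detail for the statistical analysis plan, on exploratory endpoints, with a log-rank test alongside and no decision resting on it. Most of that is correct and makes the point minor. It does not remove it. Section 8.2.1 states the formula and says that it specifies the analysis there, so a different interval in the analysis plan would depart from the protocol rather than add detail to it. The log-rank test gives no interval for the risk difference.

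Three stronger readings might be inferred, and none is supported.
- *Rare events in general get intervals that are too short.* They do not. At equal very low rates the interval over-covers. Once both risks are about 1% or more, coverage is close to 95%. The marked shortfall needs unequal rates and about one expected event or fewer in the lower arm.
- *The rule manufactures false significance.* Type I error stays at or below about 5.2%. For 0 versus 4, Fisher's exact test gives p = 0.124, but that test is conservative here. Pearson's chi-square is 0.01²/(2 × 0.005 × 0.995/400) = 4.02, p = 0.045, and a log-rank approximation gives about the same. The Greenwood step is not what makes that table nominally significant.
- *The primary result is at risk.* At 17% versus 26% coverage is 94.9%.

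It is also fair to object to a broad remedy. A switch at fewer than 10 events in either arm would apply in 99.8% of trials at 1 versus 2%, where the stated interval already covers 95.0%.

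**Conclusion.** The point holds as a narrow defect of a stated rule. The failure with no events follows from the algebra and needs no assumed rate. One empty arm is given no uncertainty, and two empty arms leave the prescribed test undefined.

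The loss of coverage depends on assumed rates. It is about 86 to 90% for 0.1 vs 0.5%, 0.25 vs 0.5% and 0.25 vs 1%, and 74.8% at the extreme of 0.1 vs 0.25%. It is about 93 to 95% for unequal pairs once the lower rate is 0.5% or more. These figures assume 400 per arm and no early censoring. Whether stent thrombosis or any component falls in the affected range cannot be told from the protocol. The trial's hypothesis of fewer events under IVUS guidance makes unequal rates plausible.

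No confirmatory conclusion, sample size or stopping decision is touched. The change is worth making because it is cheap and is best fixed before data are seen.

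**What to change.** Keep formulas (2) to (5) for the primary endpoint and for other endpoints with adequate events. Add one sentence to section 8.2.1: when either arm has zero or very few events at the time point (for example two or fewer), the risk-difference interval is a hybrid-score (Newcombe/MOVER) interval built from single-arm score limits, and the formula (5) p-value is not reported, only counts and the interval. The sentence should also name the sample size that enters the score limits under censoring, because an arm without events has no Greenwood variance from which to derive one. The number still under observation at the time point is a conservative choice.

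The two-event threshold is a convention. Applied as a switch in the enumeration above, to all pairs formed from 0.1, 0.25, 0.5, 0.75, 1, 1.5, 2 and 3% with 400 per arm, it gives coverage of at least 94.6%.

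The cost is minor programming and somewhat conservative, slightly wider intervals for exploratory endpoints. For 2 versus 8 events, for example, the interval becomes -3.43 to +0.13 points instead of -3.04 to +0.04.

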### 8.3. Sample Size Determination

Based on previous literature, an event reduction is assumed of at least 35% in the PoCE by using IVUS guidance in Left Main PCI. Based on data of the Excel trial, the expected 2-year PoCE in the IVUS guidance arm is assumed to be 17%, whereas PoCE in the angiographic guidance arm is assumed to be 26%.

The cross-over rate from angio-guidance to IVUS guidance is assumed to be 4%, and the cross-over rate from IVUS guidance to angio-guidance 3%. Taking these cross-over rates into account and using a Z (standard normal) test for the difference between two proportion, a two-sided type I error of 0.05, approximately 789 participants are needed to demonstrate superiority of an IVUS-guided approach versus a qualitative angio-guided approach in the setting of left-main PCI with a statistical power of 80%. A sample size of 2 x 400 participants allows for an attrition rate of 6%.

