| Sample size           | Based on previous literature  , we expect an event reduction of at least 35% in the PoCE by using IVUS-guidance in Left Main                                                                                                                                                                                                                                                                                                                                                                                                                                                                                                                                                                                                                                                                                                                                                                                                                                                                                                                                                                                                                                                             |

PCI. Based on the EXCEL trial , the expected 2-year PoCE event rate in the IVUS guidance arm is assumed to be 17%, whereas PoCE in the angiographic guidance arm is assumed to be 26%. The cross-over rate from angio-guidance to IVUS guidance is assumed to be 4%, and the cross-over rate from IVUS guidance to angio-guidance 3%. With a two-sided type I error of 0.05, approximately 789 patients are needed to demonstrate superiority of an IVUS-guided approach versus a qualitative angio-guided approach in the setting of left-main PCI with a statistical power of 80%. A sample size of 2 x 400 patients allows for an attrition rate of 6%.

---

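### The sample-size paragraph contradicts itself: if about 789 participants are needed, 800 allows 1.4% attrition rather than 6%; 6% attrition from 800 leaves 752

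*Protocol*

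**What the plan says.** Section 8.3 assumes for the 2-year primary composite that "the expected 2-year PoCE in the IVUS guidance arm is assumed to be 17" per cent and that "PoCE in the angiographic guidance arm is assumed to be 26" per cent. It then says "The cross-over rate from angio-guidance to IVUS guidance is assumed to be 4" per cent and "the cross-over rate from IVUS guidance to angio-guidance 3" per cent. The calculation is described as "using a Z (standard normal) test for the difference between two proportion"s, with a two-sided type I error of 0.05 and 80% power. The result is "approximately 789 participants are needed to demonstrate superiority of an IVUS-guided approach". The next sentence reads "A sample size of 2 x 400 participants allows for an attrition rate of 6" per cent. The sample-size entry of the Protocol Outline gives the same figures, ending "A sample size of 2 x 400 patients allows for an attrition rate of 6" per cent.

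Neither place says whether a continuity correction was used, or whether 789 is counted before or after attrition.

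**The concern.** Read in order, the two sentences say that 789 participants deliver the stated power and that 800 is that number with room for 6% loss. The gap between 789 and 800 is far too small for that.

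This paragraph is the protocol's only justification of size and power. The modified intention-to-treat set (section 8.1.1) drops randomised participants who do not undergo PCI, and participants who are lost or withdraw are not replaced (sections 5.14 and 5.15). A reader who wants to judge whether observed losses are tolerable needs one evaluable target. The text offers two, 789 and 752, which differ by 37. Section 8.2.1 refers statistical methods, analysis and missing data to the SAP, but the protocol itself fixes both of these sample-size figures, so the conflict has to be settled here.

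**Working it through.** **Inputs (section 8.3; allocation from section 3).** Angiography arm 26%, IVUS arm 17%; cross-over 4% from angiography to IVUS and 3% from IVUS to angiography; two-sided alpha 0.05 (z = 1.96); power 80% (z = 0.8416); 1:1 allocation; 800 randomised; 6% attrition; stated need 789.

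**Step 1. The two stated figures against each other (no method needed).**
- Margin if 789 are needed: 800 − 789 = 11, and 11/800 = 1.4%.
- Number left after 6% attrition: 800 × 0.94 = 752, which is 37 below 789.
- Number to randomise for 789 after 6% attrition: 789/0.94 = 839.4, about 840.

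**Step 2. Trying to reproduce 789 from the stated inputs.** Rates after cross-over:
- Angiography: 0.26 × 0.96 + 0.17 × 0.04 = 0.2564
- IVUS: 0.17 × 0.97 + 0.26 × 0.03 = 0.1727
- Difference: 0.0837 (= 0.09 × 0.93)

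Unpooled Z test, total N = 2 × (1.96 + 0.8416)² × (0.2564 × 0.7436 + 0.1727 × 0.8273) / 0.0837² = 747.4.

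The other route computes N without cross-over and multiplies by 1/(1 − 0.04 − 0.03)² = 1/0.8649. Unpooled: 646.3/0.8649 = 747.3. Pooled: 651.8/0.8649 = 753.6.

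The continuity-corrected number per arm is (n/4) × [1 + √(1 + 4/(n × d))]², with n the uncorrected number per arm and d the difference.

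| Total N | Unpooled | Pooled |
|---|---|---|
| Plain Z, diluted rates | 747.4 | 752.8 (754 after rounding up each arm) |
| Plain Z, inflated by 1/0.8649 | 747.3 | 753.6 |
| Continuity-corrected, diluted rates | 794.4 | 799.9 |
| Continuity-corrected, inflated by 1/0.8649 | 797.8 | 804.2 |
| Plain Z, diluted rates, divided by 0.94 for attrition | 795.1 | 800.9 |

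The plain Z test therefore gives 747 to 754, and the corrected test 794 to 804. Leaving out cross-over (652) or testing one-sided (594) does not fit either. The figure of 789 is not reproduced.

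**Step 3. Which figures fit together.** Power at the diluted rates, pooled form: 80.0% at 752, 81.8% at 789, 82.3% at 800 (80.2% at 752 in the unpooled form). So 752, 6% and 800 agree by two separate routes, the power formula and 800 × 0.94.

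**Step 4. Match to the planned test.** The primary test in section 8.2.1 divides the risk difference by the square root of the summed squared Greenwood standard errors. That is an unpooled Z with no continuity correction, so the plain formula is the one that corresponds to it.

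**Step 5. If a continuity correction was used after all.** A 6% allowance would then need 794.4/0.94 = 845 to 804.2/0.94 = 856 randomised, and 800 would leave almost no allowance.

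**The case against.** A reader might infer that 789 is simply a miscalculation and that 752 is the true figure. The documents do not establish that. The conflict shows only that the 789, the 6% or the label on 789 is wrong.

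- 789 may come from a calculation that the text does not describe. It lies within 3% of the continuity-corrected range. Taking the 35% reduction literally gives an IVUS rate of 0.26 × 0.65 = 16.9% instead of 17%, and continuity-corrected totals of 776 to 786. The protocol says approximately 789 and prints rounded inputs. Against this, no variant gives 789, no correction is mentioned, and the 6% would then be the wrong statement.
- 789 may already include some loss. For example, 750/0.95 = 789, but a 5% loss appears nowhere in the protocol, so this is number-matching and not evidence. Even if it were so, 789 would be mislabelled as the number needed for 80% power.

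A reader might also infer that 6% attrition leaves the trial 37 participants short and underpowered. That does not follow. Under the plain Z test, 752 gives 80.0%. The primary analysis uses Kaplan-Meier estimates, so participants lost during follow-up contribute until censoring. Assuming a constant hazard and 6% lost evenly over two years, 800 randomised carry about the information of 775 complete participants, or about 81% power. Participants excluded before PCI would still count in full.

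Finally, the randomised number, alpha, endpoint and decision rule do not depend on 789, and the protocol ties no action to it. All of this limits the severity. None of it makes the two sentences agree.

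**Conclusion.** The point holds as an internal contradiction, stated in both section 8.3 and the Protocol Outline. As an evaluable requirement, 789 allows 1.4% attrition from 800, and the stated 6% leaves 752. The likeliest consistent set is 752, 6% and 800, because the stated inputs with the stated test give 747 to 754 and the primary test carries no continuity correction. That remains an inference: the origin of 789 cannot be settled from the protocol.

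Severity is minor to moderate. Given the protocol's event rates and cross-over and an uncorrected Z test, power stays at about 80% with 752 evaluable participants, so the fault lies in the stated justification and not in the design. The exception would be a continuity-corrected requirement, under which the 6% allowance could not be met from 800.

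**What to change.** Correct section 8.3 and the sample-size entry of the Protocol Outline together. State the formula, whether a continuity correction was used, and whether the number needed is before or after attrition.

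- **If the stated uncorrected Z test is what was meant:** give the need as about 752 evaluable participants (376 per arm), and keep 800 randomised with 6% attrition (800 × 0.94 = 752, power 80%).
- **If 789 is kept as an evaluable need from another method:** name the method, change the allowance to 1.4%, and give the power at 752.
- **If 789 already includes attrition:** relabel it, state the loss rate used and the evaluable number behind it, reconcile that with the 6%, and give the power at 752.

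The cost is a corrected sentence or two in two places. Enrolment need not change.
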